#### 2.5.4. Energy and Nutrient Intake

The study dietitian will administer 3-day 24 h dietary recalls. Subjects will be asked about the food and beverages consumed in the past 24 h. Other details will include the meal time, type of food and beverage, cooking method, and quantity or portion size. On the day of the visit, a 24 h dietary recall will be obtained. The research dietitian will later interview the subjects via phone calls to obtain another 2 days of 24 h dietary recalls. The 3 days of 24 h dietary recalls will be on nonconsecutive days (2 weekdays and 1 weekend).

Energy and nutrient intake calculations will be performed by the Nutritionist Pro software (V.5.1.0, Axxya Systems, Redmond, WA, USA). The serving size of the food and data on energy and nutrients will be obtained from the Nutrient Composition of Malaysian Foods database on the Nutritionist Pro software. If the food or beverage is not listed in the Malaysian food database, data will be obtained from the Singapore Food Composition database [29] and the U.S. Department of Agriculture database [30]. Recipes for local cuisine or mixed dishes will be created if they are unavailable on all databases. The average of 3-day dietary recalls will be obtained to determine the mean intake of energy and nutrients, including carbohydrates, protein, fat, fibre, vitamins, and minerals.

#### 2.5.5. Lifestyle Practices

The lifestyle practices include dietary supplements, sleep duration, stress level, physical activity and smoking habit. Subjects’ frequency and dosage of dietary supplements will be obtained using a questionnaire adapted from the Malaysian Adult Nutrition Survey [21]. Sleep duration will be reported as the total hours of sleep in an average 24 h period over the past month [31]. The study will assess subjects’ stress levels using the 10-item Perceived Stress Scale (PSS-10) [32], which was validated in Malaysian T2D patients [33]. Physical activity level will be assessed using the International Physical Activity Questionnaire-Short Form (IPAQ-SF) [34]. We will use the Global Adult Tobacco Survey to assess smoking habits and second-hand smoking exposure (at home, work, public transport, and closed public areas) among subjects [35].

#### 2.5.6. Anthropometric and Clinical Measurements

Height will be measured using a stadiometer (SECA model 206, Vogel & Halke GmbH & Co., Hamburg, Germany). Subjects will be asked to remove their outer attire and shoes and empty their pockets, then stand with their back to the stadiometer while looking straight ahead. Measurements will be recorded to the nearest 0.1 cm. A body composition monitor will be used to measure the body weight and body fat percentage (Tanita Health Equipment Ltd., Tokyo, Japan). BMI will be calculated and categorised according to the World Health Organization (WHO) classification [36]. We will measure waist and hip circumferences using a measuring tape (SECA model 203, Vogel & Halke GmbH & Co., Hamburg, Germany), and the waist-to-hip ratio will be categorised according to WHO [37]. A hand dynamometer will be used to measure grip strength (JLW Instruments, Chicago, IL, USA), and the mean grip strength will be compared with the consolidated grip strength reference values [38]. Blood pressure will be measured using a blood pressure monitor (OMRON Corporation, Kyoto, Japan) and categorised according to the Adult Treatment Panel (ATP III) guidelines [39].

#### 2.5.7. Biochemical Profile

Subjects will be asked to fast overnight for 8–12 h prior to blood collection. Fasting venous blood samples will be drawn by a trained phlebotomist. Blood samples for conventional biochemical parameters (glucose, HbA1c, insulin, and lipid profile) will be transported to an established commercial laboratory for analysis (Clinipath Sdn. Bhd., Bangsar, Malaysia). Venous blood will be drawn at 2 h following the administration of a 75 g glucose solution drink to obtain the postprandial glucose level.

#### 2.5.8. Metabolomic Profile

NMR sample preparation for plasma and urine will be performed according to published protocols [40,41]. About 2 mL of the fasting blood will be collected into lithium heparin tubes, centrifuged at 1500× *g* for 20 min, divided into aliquots, frozen in a liquid nitrogen tank, and stored at −80 °C until further analysis. Subjects will also have to collect mid-stream urine into a urine container. Sodium azide 0.1% will be added to the urine sample to prevent microbial growth. The urine samples will be centrifuged at 1500× *g* for 10 min, divided into aliquots, and stored at −80 °C until further analysis.

Upon thawing, 500 μL of plasma will be vortexed for 1 min, then centrifuged for 2 min at 5000× *g* to remove solid debris. We will transfer 400 μL of plasma supernatant into a 0.5 mL ultra-centrifugal filter and centrifuged at 6000× *g* for 30 min to remove macromolecules, including lipids and proteins. We will mix 200 μL of plasma filtrates with 400 μL of phosphate buffer solution (potassium dihydrogen phosphate Kh_2_Po_4_]) prepared in deuterium oxide (D_2_O) containing 0.1% trimethylsilyl propanoic acid (TSP) and 0.1% imidazole). A total of 600 μL of prepared samples will be transferred to 5 mm NMR tubes. For urine, 400 μL of thawed sample will be added to 200 μL of phosphate buffer solution, then centrifuged at 4800× *g* for 5 min before being transferred to NMR tubes.

The nontargeted metabolomic analysis will be performed using a ^1^H-NMR platform. ^1^H-NMR spectra will be acquired using a 500 MHz NMR spectrometer (Varian Inc., Palo Alto, CA, USA). Spectral data will be preprocessed using Chenomx NMR suite software version 9.0 (Chenomx Inc., Edmonton, AB, Canada) by Fourier transformation, auto-phasing, and auto-baseline correction. Spectral data will be divided into 1000 equal bins, digitised into a table of common integral, and exported as a text file for multivariate data analysis.

Multivariate data analysis of the processed spectra will be performed using SIMCA-P+ version 15.0 (Sartorius Stedim, Umeå, Sweden) by applying various statistical algorithms including principal component analysis (PCA), partial least square discriminant analysis (PLS-DA), and orthogonal projections to latent structures discriminant analysis (OPLS-DA) to determine differences in metabolites between the three groups. Based on the multivariate data analysis results, parts of the spectra (ppm) responsible for the differences between groups will be quantified using Chenomx software by matching the corresponding peak with the metabolite database. PCA score and loading plots will be drawn in SIMCA-P+ software to validate the data obtained from Chenomx software. Pathway identification will be based on the Kyoto Encyclopedia of Genes and Genomes (KEGG) (Kanehisa Laboratories, Kyoto, Japan).

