As the nutritional assessments have shifted the focus on dietary patterns, we need to identify biomarkers of dietary patterns via the metabolomics approach. Metabolomics is a tool to measure the full profiles of low-molecular-weight metabolites in biofluids such as blood plasma and serum and urine [12]. Metabolites that can predict the transition from GDM to T2D at postpartum have been identified in various studies, including branched-chain amino acids (BCAAs), hexoses, fatty acids, sphingomyelins, and carnitines [13,14,15,16,17,18]. Nevertheless, most of these studies were limited to Western populations and did not include Asian ethnic groups.

The application of metabolomic techniques in nutrition research has led to the emerging concept of nutritype [19]. Nutritype refers to the expression of overall dietary intake in metabolites and can be used to classify individuals into a specific dietary pattern based on their metabolomic profile [19]. In other words, dietary patterns are analysed together with metabolomic profiles to identify the nutritype signatures of the study population [19].

While the roles of dietary patterns and metabolomics in determining T2D risk are significant, these two parameters have usually been separately studied. Current evidence on the combination of dietary patterns and metabolomic profile (nutritype signatures) in women post-GDM has been inconclusive, with varying results being reported [14,15,16,17]. All of the four studies only focused on specific components of dietary patterns and their metabolomic markers, such as cooking fat and oil [14], dietary fatty acids [15], glycaemic load [16], and dietary BCAAs [17]. None of the studies observed dietary patterns in their entirety. The scant evidence indicates a gap in the knowledge and a pressing need for further studies on nutritype signatures to capture the exposure to T2D in women post-GDM.

This paper describes the protocol of the Malaysian Nutritype (MyNutritype) study, including the methodology, research workflow, outcome measures, and statistical analysis. The study aims to investigate the association between dietary patterns, metabolomic profile, and T2D in women post-GDM.

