### 2.3. Study Population

The study will include Malaysian women aged 18–49 years with a previous diagnosis of GDM. Exclusion criteria will be the following: pregnant women, recent hospitalisation within the last 6 weeks, and previously diagnosed medical problems (such as type 1 or type 2 diabetes, cancer, and liver or renal disorders). The sample size will be estimated using the mean difference formula [20]. Based on a study that compared dietary intake and metabolomic profile in NGT, prediabetes and metabolomic profile in women post-GDM in Gothenburg, Sweden [14], considering a 95% confidence level and 80% power, a total of 99 subjects will be needed for the study. To account for nonresponse or refusal to participate, an additional 20% of subjects will be required, leading to a minimum of 126 subjects.

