#### 2.5.1. Diagnosis of Type 2 Diabetes and Prediabetes

After an overnight fast of 8–12 h, subjects will undergo a 75 g, 2 h OGTT. Blood and urine samples will be taken for HbA1c, insulin, lipid profile, and metabolomic analysis. Subjects will be grouped into either NGT, prediabetes or T2D based on their OGTT and HbA1c results, as advised by the study endocrinologist. Our diagnostic criteria for T2D and prediabetes are based on the Malaysian Clinical Practice Guidelines [7] (Table 1).

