## Figures and Tables

**Figure 1 metabolites-12-00843-f001:**
[figure not shown]
Research workflow.

**Table 1 metabolites-12-00843-t001:** Diagnostic values for normal glucose tolerance, type 2 diabetes, and prediabetes based on oral glucose tolerance test and HbA1c.

Category	Oral Glucose Tolerance Test		HbA1c (%)
	Fasting Plasma Glucose (mmol/L)	2-h Plasma Glucose (mmol/L)	
Normal glucose tolerance (NGT)	<6.1	<7.8	<5.7
Prediabetes, which includes: Impaired fasting glucose (IFG) Impaired glucose tolerance (IGT)	6.1–6.9	7.8–11.0	5.7–<6.3
Type 2 diabetes (T2D)	≥7.0	≥11.1	≥6.3

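### Fasting glucose helps define the glycaemic groups and is not stated to be excluded from the fasting NMR profile modelled against them, so part of the T2D-associated profile may restate the diagnosis

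*Protocol article*

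**What the plan says.** **Outcome.** Section 2.5.1 states: "Subjects will be grouped into either NGT, prediabetes or T2D based on their OGTT and HbA1c results". Table 1 is headed "Diagnostic values for normal glucose tolerance, type 2 diabetes, and prediabetes based on oral glucose tolerance test and HbA1c" and gives three limits per group. For fasting glucose they are <6.1, 6.1–6.9 and ≥7.0 mmol/L. Section 2.3 excludes women already diagnosed with type 1 or type 2 diabetes, so T2D status comes from the study's own tests.

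**Predictors.** In the same paragraph as the OGTT, after one overnight fast, section 2.5.1 says "Blood and urine samples will be taken for HbA1c, insulin, lipid profile, and metabolomic analysis". Section 2.5.8 specifies fasting plasma, filtered to take out macromolecules, and urine. After Fourier transform and automatic phase and baseline correction, "Spectral data will be divided into 1000 equal bins, digitised into a table of common integral, and exported as a text file". No spectral region is stated to be dropped.

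**Use.** The bins enter PCA, PLS-DA and OPLS-DA "to determine differences in metabolites between the three groups". Regions that drive the differences are matched to metabolites and quantified, and pathways are identified (section 2.5.8). Section 2.5.9 builds the nutritype signatures from the NMR profile, and section 2.7 tests them against T2D by multinomial logistic regression.

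**The concern.** One analyte stands on both sides of the analysis. Fasting plasma glucose helps decide which group a woman belongs to. Glucose is a small molecule that no described preparation step removes, so it should also be present in the fasting plasma spectrum, and it may be present in urine. A supervised method asked to separate the groups will favour it.

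At stake is aim (b), the metabolomic profile associated with T2D and prediabetes. The primary outcome, the nutritype signatures associated with T2D, is affected as far as glucose enters a signature. The part of an association that glucose contributes by definition is not evidence about diet or a new biomarker. The Introduction lists earlier markers "including branched-chain amino acids (BCAAs), hexoses, fatty acids, sphingomyelins, and carnitines", but those were reported as predicting a later transition from GDM to T2D. Here a glucose signal would be set against a diagnosis made at the same work-up.

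**Working it through.** **Step 1. Tracing the definitions**

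| Link | Source | Content |
|---|---|---|
| Known diabetes excluded | 2.3 | T2D status rests on study tests |
| Grouping | 2.5.1, Table 1 | fasting glucose, 2-h glucose, HbA1c |
| Timing | 2.5.1 | metabolomic samples described with the OGTT |
| Matrix | 2.5.8 | fasting plasma, and urine |
| Removed in preparation | 2.5.8 | macromolecules from plasma; nothing that removes glucose |
| Bins | 2.5.8 | 1000, no stated exclusion |
| Supervised models | 2.5.8 | the same three groups |
| Final test | 2.7 | signatures against T2D |

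The chain closes for aim (b). For the signatures it depends on step 3 of section 2.5.9, which can be read in two ways:
- If the PLS-DA classes are the coded dietary scores, glucose enters a signature only where it differs between dietary classes. Its later association with T2D is then still partly definitional.
- If the classes are T2D and non-T2D, which the closing phrase of that step suggests, glucose can enter because of the outcome itself.

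**Step 2. Group size for an illustration**

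The article gives no figure on this point. Its minimum of 126 is reproduced by 99/3 = 33 per group, 33/(1 − 0.20) = 41.25, rounded up to 42, and 3 × 42 = 126. The point does not depend on this number; it only supplies the 42 per group used below.

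**Step 3. Illustration on assumed inputs**

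None of the following comes from the documents except the Table 1 limits, the 1000 bins and the group size.
- Fasting glucose = exp(ln 5.3 + 0.13 z₁), 2-h glucose = exp(ln 7.0 + 0.30 z₂), HbA1c = exp(ln 5.5 + 0.09 z₃), with pairwise correlation ρ of the z's.
- T2D if any one marker reaches its T2D limit; otherwise prediabetes if any reaches its prediabetes limit; otherwise NGT.
- NMR glucose = fasting glucose × exp(c·z), with c = 0.05 or 0.15.
- 20 or 50 of the 1000 bins carry glucose; every other bin is pure noise.
- One-component PLS-DA of T2D (n₁ = 42) against non-T2D (n₀ = 84), with weights proportional to Zᵀ(y − ȳ), 7-fold cross-validation and 60 runs per setting. AUC = [R₁ − n₁(n₁+1)/2]/(n₁n₀), where R₁ is the rank sum in the T2D group.

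Mean results (where two values are shown, they are the range over 20 and 50 glucose bins):

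| ρ | c | AUC, glucose alone | AUC, bins kept | AUC, bins removed | Glucose share of top 20 bins |
|---|---|---|---|---|---|
| 0.3 | 0.05 | 0.69–0.70 | 0.67–0.69 | 0.50–0.51 | 84–96% |
| 0.3 | 0.15 | 0.64 | 0.61–0.63 | 0.50 | 53–61% |
| 0.5 | 0.05 | 0.78–0.79 | 0.76–0.77 | 0.47–0.50 | 100% |
| 0.5 | 0.15 | 0.70 | 0.67–0.69 | 0.50–0.52 | 83–92% |
| 0.7 | 0.05 | 0.86 | 0.85 | 0.50–0.51 | 100% |
| 0.7 | 0.15 | 0.75 | 0.72–0.74 | 0.49–0.50 | 96–98% |

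The drop to chance after removal follows from making all other bins noise, so it predicts nothing about the real spectra. What the exercise shows is narrower. A spectrum with no information beyond glucose would still cross-validate as associated with T2D, and cross-validation does not reveal the overlap, because the overlap lies in the outcome definition.

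**The case against.** The strongest reply is that retention of glucose is read from silence. The article is condensed. It also does not say how the water region, or the TSP and imidazole added to the buffer, are handled, and a fuller document may exclude regions. This stands as a limit on certainty: the article does not say in words that glucose is kept. It does not dispose of the point, because nothing shown excludes glucose, and dropping an endogenous metabolite from a non-targeted profile is a deliberate choice that silence does not imply.

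Second, the overlap would be visible. Discriminating regions are matched to named metabolites, and the article claims associations only. That is fair: glucose labelled as glucose is a harmless positive check. The difficulty begins when it is counted in the T2D-associated profile or carried into a signature.

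Third, deleting equal-width bins also deletes any metabolite that shares them. This stands, and it is why removal should not be the only analysis.

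A reader might also infer more than the documents support:
- **Near-perfect separation**, because the NGT and T2D fasting limits do not meet. The prediabetes band lies between them, 2-h glucose and HbA1c also classify, and the share of women classified by fasting glucose is not given. Even the illustration reaches only 0.64 to 0.86.
- **A known number of affected bins.** The documents give no basis for one.
- **That every nutritype signature is circular.** This depends on the ambiguous step 3 in section 2.5.9.
- **That weaker metabolites will be masked.** This is possible, but not shown.

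**Conclusion.** The concern holds as a partial circularity. Followed as written, the plan lets an analyte that helps define the groups contribute to their separation, to the ranking of metabolites and to pathway output, and to the T2D association of any signature that includes it.

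Its size cannot be derived from the documents. The AUC range of 0.61 to 0.85 with glucose bins kept describes assumed inputs only, including that any single criterion suffices for classification.

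The conclusion rests on two readings of the article: that the diagnostic and metabolomic samples come from the same work-up, as section 2.5.1 describes them, and that no unstated step removes glucose signals. It is a cheap improvement to the analysis plan and changes no sample-size figure.

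**What to change.** In sections 2.5.8, 2.5.9 and 2.7, prespecify before the spectra are modelled that:

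1. every model with glycaemic group or T2D as outcome is run with and without the plasma and urine glucose signals, meaning both the bins and quantified glucose;
2. conclusions about T2D-associated metabolites and nutritype signatures rest on what persists without glucose;
3. glucose itself is reported as a positive check on the assay and the grouping.

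The cost is a short addition to the text and a second run of each model, with no new samples or visits. Group separation will look smaller in the glucose-free version, and metabolites that overlap the glucose bins are lost there. Showing both versions lets the reader see each effect.

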## 1. Introduction

Type 2 diabetes (T2D) has reached epidemic proportions in Asia, with the Western Pacific Region contributing to 38% of T2D cases worldwide [1]. Malaysia is the fifth leading country in the Western Pacific Region with the highest prevalence of T2D [1]. The prevalence of T2D in Malaysia has increased by almost 60% over a 10-year period, partly due to a rising prevalence of overweight and obesity, physical inactivity, and dietary practices that include a low intake of fruits and vegetables and high intake of sugar-sweetened beverages [2].

Women previously diagnosed with gestational diabetes mellitus (post-GDM) had a nearly 10-fold relative risk of T2D compared with those with normoglycemic pregnancies [3]. Hence, early identification and intervention are critical to preventing T2D in this high-risk group. Risk factors of T2D in women post-GDM include high prepregnancy body mass index (BMI), sedentary behaviour, and an unhealthy dietary pattern low in carbohydrates but high in animal protein and fat [4,5,6]. Current recommendations support diabetes screening at 6 weeks postpartum via oral glucose tolerance test (OGTT) and/or HbA1c after GDM [7]. However, diabetes screening conventionally does not include nutritional assessments, even though an unhealthy diet is highly relevant in expediting disease progression in women post-GDM [6].

Regarding dietary patterns, adherence to healthful dietary patterns such as the alternate Mediterranean Diet (aMED) was associated with a lower risk of T2D in women post-GDM [8]. The Mediterranean diet is widely acknowledged as a healthy dietary pattern, characterised by high intakes of vegetables, fruits, nuts, grains, legumes, fish, and olive oil [9]. Malaysian adults consume a diet high in fish and green leafy vegetables, yet simultaneously high in rice, sugar, animal protein, and fat [10,11], showing a dissimilarity with dietary patterns commonly practiced in the Western population. Limited research has been conducted on the association between Malaysian-tailored dietary patterns and T2D risk in women post-GDM.

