### 2.1. Design

This is a comparative cross-sectional study involving women post-GDM, named the Malaysian Nutritype (MyNutritype) study. The primary outcome is the nutritype signatures associated with T2D in Malaysian women post-GDM. The secondary outcomes of the study include the comparisons of anthropometric and clinical measurements, biochemical profile, energy and nutrient intake, and lifestyle practices between the three groups of women post-GDM (NGT, prediabetes, and T2D).

The aims of this study are:(a)To determine dietary patterns associated with T2D and prediabetes;(b)To determine the metabolomic profile associated with T2D and prediabetes using one-dimensional proton nuclear magnetic resonance (^1^H NMR) spectroscopy;(c)To identify nutritype signatures (association between dietary patterns and metabolomic profile);(d)To determine the nutritype signatures associated with T2D in women post-GDM;(e)To compare other parameters in women post-GDM with normal glucose tolerance (NGT), pre-diabetes and T2D, which include:i.Anthropometric and clinical measurements;ii.Biochemical profile;iii.Energy and nutrient intake;iv.Lifestyle practices.

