### 2.7. Statistical Analysis

Statistical analysis will be performed using SPSS statistical software version 25.0 (IBM, Chicago, IL, USA). Data for categorical variables will be reported as number and percentage, while continuous data will be reported as mean ± standard deviation (SD). Data normality will be assessed prior to data analysis. The study will analyse the differences in the demographic characteristics between subjects who agreed to participate in the study versus those who did not agree to participate. Pearson’s correlation coefficient test will be used to determine correlations between continuous variables, the Chi-squared test to determine the association between categorical variables, and one-way analysis of variance (ANOVA) to compare the differences between the three groups. Multivariate linear regressions will determine the association between the metabolomic profile and factor scores of each dietary pattern yielded from PCA. Multinomial logistic regression will determine the factors, and the nutritype signature models associated with T2D. Variables significant at the bivariate level will be entered into the regression model as confounders. Crude and adjusted odds ratios (ORs) with a 95% confidence interval (CI) will be presented. Subgroup analyses will also be performed, such as early versus late postpartum (<1 year versus ≥1 year post-GDM), supplement versus nonsupplement users, and obese versus nonobese subjects. A previous study found different risk factors of T2D at early (<1 year) versus late postpartum (≥1 year) following GDM [4]. In case of missing data, the study will report the number of available data for the variable. We will analyse any differences in the characteristics between reporters versus nonreporters. A *p*-value < 0.05 for all statistical tests will be considered significant.

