Metabolomic profiles associated with dietary patterns have been previously studied in women post-GDM [14,15,16,17]. In the study by Andersson-Hall et al. involving 237 Scandinavian women post-GDM, linoleic acid was positively associated with vegetable oil and negatively associated with margarine intake. The linoleic acid level was reduced in women post-GDM who transitioned to T2D [14]. However, food intakes were calculated as the proportion of total diet (%) and not their absolute values in the study [14]. Another study involving 347 women post-GDM from the Nurses’ Health Study II found a correlation between dietary and plasma BCAAs [17]. Additionally, women post-GDM with higher dietary and plasma BCAAs had an elevated risk of T2D [17]. Serum and dietary polyunsaturated fatty acids were also correlated in the German study by Fugmann et al.; however, this study did not correlate dietary and serum fatty acids with the risk of T2D [15]. One study did not find any association between dietary glycaemic index and metabolites and did not assess the correlation between these parameters with the risk of T2D [16]. All of these studies [14,15,16,17] only focused on specific types of food or dietary components, instead of exploring dietary patterns as a whole. Only two studies [14,17] directly associated dietary intake and metabolites with the risk of T2D, indicating a paucity of evidence concerning nutritype signatures. Furthermore, all of these studies were conducted in the Western population, whose metabolomic profile may differ from that of the Asian population [49]. For instance, White European pregnant women had significantly lower glucose levels and most amino acid metabolites compared with South Asians, due to differences in body mass index and characteristics during pregnancy [49].

This study has a few limitations. The nature of the study is cross-sectional. Hence, the study will not be able to establish causation and effect. The study is limited to exploring only associations between dietary patterns, metabolomic profile, nutritype signatures, and T2D at a single time point. We also will not stratify subjects according to whether they have been practising certain treatments for T2D.

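### Metabolites that separate the glycaemic groups (aim b) are selected with no covariate, so some that track BMI could be reported as the T2D profile; BMI-adjusted models shown beside the unadjusted results would be a cheap improvement.

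*Protocol article*

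**What the plan says.** Aim (b), in section 2.1, is "To determine the metabolomic profile associated with T2D and prediabetes using one-dimensional proton nuclear magnetic resonance" spectroscopy. Section 2.5.8 gives the analysis: PCA, PLS-DA and OPLS-DA, used "to determine differences in metabolites between the three groups". The output is carried forward directly: "parts of the spectra (ppm) responsible for the differences between groups will be quantified using Chenomx software", followed by pathway identification. The glycaemic group label is the only input named besides the spectra.

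Adjustment appears in section 2.7: "Variables significant at the bivariate level will be entered into the regression model as confounders". The regression on T2D described there is multinomial and concerns the factors and the nutritype signature models, with crude and adjusted odds ratios. An obese versus nonobese subgroup analysis is also listed. Neither is tied to the selection in section 2.5.8, and BMI is nowhere fixed as an adjustment variable.

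On BMI, the Introduction states "Risk factors of T2D in women post-GDM include high prepregnancy body mass index (BMI), sedentary behaviour" among others. The Discussion reports lower glucose and lower levels of most amino acid metabolites in White European than in South Asian pregnant women, "due to differences in body mass index and characteristics during pregnancy". Current BMI (section 2.5.6), and pre-pregnancy weight, age and ethnicity (section 2.5.2), are all collected.

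**The concern.** If the women with T2D are heavier on average, a metabolite that rises or falls with BMI will differ between the glycaemic groups even if it has no relation to glycaemia at a given BMI. A discriminant method given only spectra and group labels cannot tell the two situations apart. Under aim (b) the selected metabolites are themselves the result, so a reader could take an adiposity marker for a marker of T2D. The article says that its findings should support early prevention measures, and for that use it matters whether a metabolite carries information beyond weight.

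**Working it through.** **1. The plan's own sample size.** The article gives 99 women before and 126 after a 20% allowance. If the three groups are equal (an assumption), 33 / (1 − 0.20) = 41.25, rounded up to 42 per group, and 3 × 42 = 126. The figure reproduces. The base of 99 cannot be recomputed, because no mean difference or SD is given. The point does not depend on it.

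**2. Inputs that the article does not give (all assumed).** BMI gap δ between T2D and other women, in SD units: 0.5 to 0.8. Within-group correlation r between BMI and the metabolite: 0.2 to 0.4. Women with T2D: 13, 25 or 33 of 126. Direct T2D effect on the metabolite: zero.

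**3. Unadjusted comparison.** With BMI = N(0,1) + δ·T2D and metabolite = r·BMI + noise of variance 1 − r², the within-group SD is 1. The expected difference is r·δ, SE = √(1/n₁ + 1/n₂), λ = r·δ / SE, and the rejection rate is approximately Φ(−1.96 + λ) + Φ(−1.96 − λ).

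| T2D / other | δ | r | r·δ | SE | λ | Rejection, formula | Rejection, simulated |
|---|---|---|---|---|---|---|---|
| 13 / 113 | 0.5 | 0.2 | 0.10 | 0.293 | 0.341 | 6.3% | 7% |
| 25 / 101 | 0.8 | 0.3 | 0.24 | 0.223 | 1.074 | 18.9% | 20% |
| 33 / 93 | 0.8 | 0.4 | 0.32 | 0.203 | 1.579 | 35.2% | 36% |

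With the BMI that drives the metabolite in the model, simulated rejection is 4% to 6%.

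**4. Three equal groups, wider assumptions.** With an NGT-to-T2D gap of 0.5 to 1.0 SD and r of 0.3 to 0.5, the unadjusted F test rejects in 7.7% to 42% of studies at 33 per group and 9.6% to 53% at 42 per group. With BMI in the model it rejects in 4.3% to 5.9%.

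**5. The selection step itself.** Simulated first-component PLS-DA at 33 per group used 1000 bins (the article's number), 50 of them related to BMI and none to T2D. BMI bins exceed a VIP of 1 in 36% to 85% of cases, against 28% to 32% for null bins. After the bins are residualised on BMI, the BMI bins pass in 30% to 33%, no more often than null bins. The VIP cut-off is an assumption, since the article states none.

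**6. The bivariate screen.** If the screen is read as a 5% test of BMI across three groups of 33, BMI enters the later regression in about 40% of studies at a gap of 0.5 SD, 81% to 83% at 0.8 SD and 94% to 95% at 1.0 SD.

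**7. Which BMI to adjust for.** Suppose current BMI drives the metabolite and only pre-pregnancy BMI is in the model, with an assumed correlation of 0.5 to 0.7 between the two. In the last two rows of the table, rejection can stay above 5%. It reaches about 11% if the pre-pregnancy gap is as large as the current one. It is 9% to 13% (25 / 101) and 13% to 23% (33 / 93) if the pre-pregnancy gap is smaller in proportion to the correlation.

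**8. What loss of significance means.** With a true direct T2D effect of 0.45 SD in the same settings, about 27% to 42% of metabolites significant without adjustment lose significance once BMI is added.

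**The case against.** The strongest reply is that aim (b) asks only for an association, and the Discussion limits the study to associations. A metabolite that differs between groups through adiposity is still associated with T2D, and BMI may lie on the pathway. This stands as a reason to keep the unadjusted result. It is not a reason to leave out the adjusted one.

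Second, section 2.7 plans adjusted odds ratios, a three-group ANOVA and an obesity subgroup; the list of algorithms in section 2.5.8 is open; and the factors in the multinomial model might include metabolites. That reading is possible but not stated. Even then, BMI would enter only after passing a screen, and the subgroup leaves BMI varying within each stratum.

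Third, this is a condensed article, and covariate models could be set out elsewhere. However, the article does say where adjustment takes place, and the selection step is not included.

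Two stronger readings are tempting, and the text does not support them. A reader might infer that the regions found in section 2.5.8 feed the nutritype signatures and hence the primary outcome. Section 2.5.9 instead takes metabolites from PLS-DA loadings of coded dietary scores on the NMR profile, and does not say that those regions are used. A reader might also infer that the article shows BMI driving metabolites in this population. It cites an ethnic comparison in pregnant women that also credits characteristics during pregnancy, and its T2D link is to pre-pregnancy BMI.

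**Conclusion.** The point holds as a low-cost improvement to aim (b). As written, the metabolites reported as the T2D profile are chosen without regard to BMI, and no later step is stated to correct this. The size cannot be determined from the article. Under the assumptions in the table, the chance that a BMI-only metabolite differs at the 5% level runs from about 6%, which is negligible, to about 36%, which is not; with BMI in the model it is about 5%. These figures rest on assumed BMI gaps, correlations and T2D counts, and on no direct T2D effect. The bin simulation also omits true T2D signals, which would compete for the top ranks. No claim is made about the nutritype signatures or the primary outcome.

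**What to change.** Keep the planned PCA, PLS-DA and OPLS-DA. For each flagged metabolite, add a linear model of its level on glycaemic group with BMI, age and ethnicity fixed in advance rather than screened. Fit it once with current measured BMI and once with pre-pregnancy BMI (recorded pre-pregnancy weight with measured height). Current BMI may over-adjust if it lies on the pathway, and pre-pregnancy BMI may leave residual confounding, so neither is enough alone.

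Report unadjusted and adjusted group differences with 95% CIs side by side, and describe how far each estimate shrinks. Do not relabel a metabolite as adiposity-related only because it loses significance; step 8 shows how often that would mislabel a real effect.

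The cost is a few extra regressions on data already collected. Where BMI lies on the pathway, the adjusted estimate shows only the part not acting through adiposity, which is why both are reported.
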